#### Secondary outcome measures

##### The change of ovarian reserve function

Assessing patients’ ovarian reserve function before and after acupuncture intervention (at 0 weeks and up to 12 weeks), including:
The serum AMH, inhibin, and FSH and E2 levels on the third day of menstruation;AFC.

##### Outcomes of IVF

Outcomes of IVF include:
Gn dosage and usage days;E2 level and endometrial thickness on human chorionic gonadotropin (HCG) day;Number of oocytes;MII oocytes;Normal fertility rate;The number of available embryos;Number of high-quality embryos;Cycle cancelation rate (including cycle cancelation rate caused by various reasons);Implantation rate: including fresh periodic implantation rate, per cycle implantation rate and cumulative implantation rate;Fresh cycle clinical pregnancy rate and cycle cumulative clinical pregnancy rate;Early, mid, and late pregnancy abortion rate;Risk of ovarian hypertrophy and incidence of obstetric complications;FSH, LH, E2, and AMH in follicular fluid; oxidative stress-related indicators such as reactive oxygen species (ROS), superoxide dismutase (SOD) level, etc.;Live rate: including fresh cycle live rate, cycle live rate and cumulative live rate.

These outcomes will be assessed through study completion, at an average of 1 year.

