### Randomization and masking

Internet-based central randomization system will be applied in this trial. Three hundred thirty-eight participants will be randomly allocated to the treatment group and control group in a 1:1 ratio. The Internet-based central randomization system designs the random parameters and allocation. The appointed researchers in each hospital will apply for the group assignment allocated by the system through inputting a specific code. The randomization protocol and the parameters set during it are collectively called blinding code, which are kept strictly by researchers who are not involved in the process of outcome evaluation and statistical analysis.

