### Sample size

According to studies conducted by Hong SB et al. and Roustan A et al., the clinical pregnancy rate of DOR patients is respectively 20.6% and 20.2% [16, 17]. Due to the lack of effective randomized blinded controlled clinical trials that choose clinical pregnancy rate per cycle as the primary outcome measure in evaluating acupuncture efficacy, we presume 15% for the patient's clinical pregnancy rate per cycle. Assuming that the clinical pregnancy rate can be increased by 15% after acupuncture treatment, *α*=0.05, *β*=0.20, power is 80%. The sample size is calculated according to the following formula [18], nA=κnB, nB=[pA(1-pA)/κ+pB(1- pB)](z1-α/2+z1-β)2/(pA-pB)2,*κ*=1, then we get nA=nB=135,which means the sample size of each group is 135. Allowing for a 20% dropout rate, the sample size of this trial is 338 participants.

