### Statistical methods

All analyses will be based on the intention-to-treat principle. Data analysis will be performed by an independent statistician using SAS statistical software (version 9.4; SAS Institute Inc.).

The analysis of variance (ANOVA) will be used to test the difference of clinical pregnancy rate (primary outcome) between the two intervention groups with the baseline date as a variate and taking into account the multicenter effect. Missing data will be imputed using the multiple imputation method. Continuous data will be presented as the mean and standard deviation, or the median and interquartile range. Categorical data will be presented as the number and percentage. Comparisons between groups will be analyzed using an independent *t* test or Wilcoxon rank-sum test for continuous variables, and a chi-square test or Fisher exact test for categorical variables. All statistical tests will be two-sided, and *p* < 0.05 will be considered statistically significant.

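### If fertilisation and implantation rates are pooled over oocytes, embryos or cycles, the only categorical tests named (chi-square, Fisher) ignore within-woman correlation

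*Protocol article*

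**What the plan says.** - **Outcomes of IVF** (secondary outcomes) lists "Implantation rate: including fresh periodic implantation rate, per cycle implantation rate and cumulative implantation rate" and "Normal fertility rate", the latter read here as the normal fertilisation rate. No denominator is given for any of them. The same list has plain counts, such as oocytes, MII oocytes and available embryos.
- **Statistical methods** sends continuous variables to a t test or Wilcoxon rank-sum test and applies "a chi-square test or Fisher exact test for categorical variables". It adds that "All statistical tests will be two-sided" at the 5% level. The only dependence it mentions is the centre effect, in the sentence on the primary outcome.
- **Primary outcome measure** contains the one rate that the article defines. Its denominator is embryo transfer cycles, not women.
- **Randomization and masking** makes the participant the randomised unit: participants are "randomly allocated to the treatment group and control group in a 1:1 ratio".

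**The concern.** Oocytes from one woman share her age, ovarian reserve, stimulation and partner's sperm, and her embryos share her uterus as well. Their results are therefore likely to be positively correlated. Chi-square and Fisher tests on pooled oocytes, embryos or cycles treat each as a separate participant. With more than one unit per woman and positive correlation, the error goes in one direction: intervals are too narrow and false positives exceed 5%.

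Per-cycle and cumulative versions can add further units from the same woman, because these outcomes are followed for about a year on average. The trial's stated aim is better ovarian function, so fertilisation and implantation results are the kind that would be cited as supporting evidence.

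**Working it through.** **The plan's own figure.** The article states no figure for these rates, only a primary-outcome size of 135 per group. The dropout step reproduces: 135 / 0.80 = 168.75, so 169 per arm and 338 in total. (As a separate matter, the printed formula with 15% against 30% gives (0.30×0.70 + 0.15×0.85) × (1.960 + 0.842)² / 0.15² = 117.7, so 118, not 135. A continuity-corrected formula gives 134. Nothing below depends on this, because the approximate inflation formula does not contain the number of women.)

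**Inputs**
- From the article: two-sided 5% level, randomisation by participant, 135 women per arm.
- Assumed, because the article does not give them: units per woman, ICC, and the underlying rates (15% for implantation, 65% or 70% for fertilisation).

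**Step 1: equal numbers per woman.** With m units per woman, the variance is understated by the design effect DE = 1 + (m − 1) × ICC. The actual two-sided error of a nominal 5% test is 2 × [1 − Φ(1.96 / √DE)].

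| Units per woman | ICC | DE | Actual type I error |
|---|---|---|---|
| 1 | any | 1.0 | 5.0% |
| 2 | 0.05 to 0.5 | 1.05 to 1.50 | 5.6% to 11.0% |
| 3 | 0.1 to 0.3 | 1.2 to 1.6 | 7.4% to 12.1% |
| 5 | 0.1 to 0.3 | 1.4 to 2.2 | 9.8% to 18.6% |

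Example: m = 3 and ICC = 0.3 give DE = 1 + 2 × 0.3 = 1.6. Then 1.96 / √1.6 = 1.55, a two-sided error of 12.1%.

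**Step 2: unequal numbers per woman.** Two beta-binomial simulations under no treatment effect applied the unadjusted two-proportion test to pooled units.

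| Outcome and assumed units per woman | Women per arm | ICC | Actual type I error |
|---|---|---|---|
| Implantation, 1-2 embryos | 135 | 0.05 to 0.5 | 5.3% to 9.2% |
| Implantation, 1-2 embryos | 120 | 0.1 to 0.3 | 6.2% to 7.5% |
| Implantation, 1-3 embryos | 135 | 0.05 to 0.5 | 5.8% to 12.2% |
| Cumulative implantation, 1-6 embryos (mean about 3) | 120 | 0.1 to 0.3 | 8.1% to 14.6% |
| Fertilisation, 1-7 oocytes | 135 | 0.05 to 0.3 | 7.1% to 16.9% |
| Fertilisation, about 4 oocytes | 120 | 0.1 to 0.3 | 9.4% to 18.1% |

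The runs with 135 women used 20,000 replicates each, and those with 120 women used 6,000. In the latter, a variance clustered on the woman brought the error back to 4.9-5.6%.

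**Step 3: cross-check.** For unequal cluster sizes, DE = 1 + (E[m²]/E[m] − 1) × ICC. The 1-7 oocyte scenario used probabilities 0.15, 0.20, 0.20, 0.15, 0.12, 0.10 and 0.08, so E[m] = 3.51, E[m²] = 15.67 and the ratio is 4.46. At ICC 0.3, DE = 1 + 3.46 × 0.3 = 2.04 and the error is 17.0%, against 16.9% simulated. The 1-2 embryo scenario used 0.4 and 0.6, so the ratio is 2.8 / 1.6 = 1.75. At ICC 0.5, DE = 1.375 and the error is 9.5%, against 9.2% simulated.

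**The case against.** A reader might infer that the plan prescribes chi-square tests on embryos and oocytes. The article does not go that far. It prints no denominators for these rates and does not assign a test to them by name. A proportion calculated for each woman (fertilised out of retrieved, say) is a continuous variable. It would go to the t test or Wilcoxon test already named, and with one value per woman there is no clustering. That part of the objection stands, so the point is conditional.

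Three further limits also stand:
- A reader might extend the point to an MII rate. The outcome list has MII oocytes among the counts, and an MII rate appears only in the Background, describing a cited study.
- The size rests wholly on assumed values. Eligibility selects women with few follicles, low AMH or fewer than 3 oocytes in their last stimulation cycle, so the scenarios with many units may be generous and the effect on fresh implantation may be small.
- These are a few of many secondary outcomes. The sample size does not rest on them, and the primary outcome has its own analysis sentence.

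It can also be said that units of analysis for secondary outcomes are commonly left to a full protocol or analysis plan. That would settle the matter if the article were silent on tests. It is not silent: it names the tests for categorical data without limiting them to one observation per woman. The text separates rates from counts and defines its one explicit rate over transfer cycles, so the pooled reading is a natural one.

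**Conclusion.** The point holds in conditional form. The named categorical tests are valid for the fertilisation and implantation rates only if each woman supplies one independent observation, and the article sets no such restriction. If the rates are pooled, a nominal 5% test has a true error of:
- about 5-9% for implantation with 1-2 embryos per woman;
- up to about 12-15% with more embryos or cumulative counting;
- about 7-18% for fertilisation.

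These ranges assume ICCs from 0.05 to 0.5 for implantation and 0.05 to 0.3 for fertilisation, together with the units per woman shown in the working. With one unit per woman, or a per-woman proportion, there is no inflation. The direction is firm under positive correlation, but the size cannot be fixed from the article. The point is worth correcting and does not touch the primary conclusion.

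**What to change.** In Statistical methods:
1. Limit chi-square and Fisher exact tests to outcomes with one value per woman.
2. State the denominator of each fertilisation and implantation rate, including the per-cycle and cumulative versions.
3. For any rate counted over oocytes, embryos or repeated cycles, name an analysis with the woman as cluster or unit. Options are a logistic GEE or a cluster-robust ratio, each with arm and centre as terms, or a per-woman proportion compared by the continuous tests already listed.
4. Report the number of women contributing to each rate in each arm.

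The choice in item 3 should be deliberate. A pooled estimate weights women by their number of oocytes or embryos, which treatment may itself change, while a per-woman proportion weights women equally. The two can therefore estimate different quantities.

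The cost is a few sentences and standard SAS procedures, with no new data collection. Intervals for these secondary rates become somewhat wider.

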##### Blood biochemical index examination before and after acupuncture

The level of blood corticotrophin-releasing hormone (CRH), norepinephrine, adrenaline, 5-hydroxytryptamine, beta-aminobutyric acid (GABA), dopamine (DA), and neuro-endorphin will be tested before and after treatment (at 0 weeks and up to 12 weeks).

##### Deqi sensation scale of acupuncture

After each acupuncture treatment, patients will be asked to rate the MASS [11] independently by evaluating 12 acupuncture sensation degrees within 5 min. The higher the weighted total score is, the more obvious is the Deqi sensation degree.

##### Questionnaires

Evaluation of anxiety, depression, and quality of life will be performed before and after treatment (at 0 weeks and up to 12 weeks), including:
Baker anxiety self-rating scale (BAI) and baker depression self-rating scale (BDI-II): higher score indicates higher degree of depression or anxiety [12, 13].Zung anxiety self-rating scale (Zung-SAS), Zung depression self-rating scale (Zung-SDS) [14, 15].Quality of life measurement (QOL): Quality of life will be assessed by SF-36 and the Chinese quality of life scale (CHQOL).

##### Follow-up detection

Pregnancy patients will be followed up to the end of pregnancy. Adverse pregnancy outcomes and live birth rates will be recorded. Non-pregnant patients will be followed up for 1 year after treatment, testing the ovarian reserve function, follow-up treatment, and pregnancy status of the patients within 1 year.

### Participant retention

All of the participants, regardless of which group, will receive health education. Health education includes: (1) patients will be encouraged to engage in an appropriate exercise training program, (2) patients will be suggested to continue striving for a healthy diet, and (3) patients will be given relaxing training and psychological counseling. For pregnant patients, 3D ultrasound will be appointed in advance and advices during pregnancy and perinatal will be given by gynecologists. Non-pregnant patients will also be followed up for 1 year after treatment and given advices about following treatment like ovulation-inducing scheme of IVF-ET.

### Adverse events

Adverse events (AEs) will be classified. AEs related with electro-acupuncture include bleeding after needle withdrawal, striking of needle, bending of needle, and fainting during acupuncture treatment. AEs related to IVF-ET include ovarian hyperstimulation syndrome, colporrhagia and infection caused by egg retrieval, and multiple pregnancy. Researchers will obtain AEs by inquiring of the participants at each treatment or follow-up visit or by voluntarily reporting by the participants. The percentage of AEs and severe adverse events that occurred during treatment will be recorded in detail. Chi-square test is used to analyze the total proportion of adverse events in each treatment regimen and the differences between the classifications. Unless otherwise formally requested, each report from the safety monitor board will report details and summaries of adverse events in a double-blind manner.

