### Objectives

Through this study, we expect to test the following hypotheses: (1) evaluate whether electro-acupuncture is superior to the control group in ameliorating ovarian function of DOR patients reflected by improving clinical pregnancy rate, and (2) assess the safety of electro-acupuncture.

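### Multiple pregnancy is counted as an adverse event, so the total and IVF-ET class comparisons can reject because the treatment raises pregnancy rather than because it harms

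*Protocol article*

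**What the plan says.** The second objective is "2) assess the safety of electro-acupuncture" (Objectives).

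The Adverse events section sets up two classes:

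- Needling: "AEs related with electro-acupuncture include bleeding after needle withdrawal, striking of needle, bending of needle, and fainting during acupuncture treatment".
- IVF: "AEs related to IVF-ET include ovarian hyperstimulation syndrome, colporrhagia and infection caused by egg retrieval, and multiple pregnancy".

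The analysis is then fixed in one sentence: "Chi-square test is used to analyze the total proportion of adverse events in each treatment regimen and the differences between the classifications". No event is excluded from the total, and no separate denominator is given for multiple pregnancy.

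Primary outcome measure defines clinical pregnancy by a fetal heartbeat at 6–7 weeks. Sample size takes a control rate of 15% and continues: "Assuming that the clinical pregnancy rate can be increased by 15% after acupuncture treatment".

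**The concern.** Only a woman who conceives can have a multiple pregnancy. If the trial succeeds as designed, more women conceive in the active arm. The multiple-pregnancy count per randomised woman then rises with them, with the same share of pregnancies multiple and no harm from the needles. That excess enters the tested total. It also enters the IVF-ET class, so splitting by class does not remove it.

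At stake is how a significant AE result is read. A difference in the total or in the IVF-ET class would look like evidence against the safety of electro-acupuncture when it may restate the efficacy result. The primary analysis is not affected.

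**Working it through.** **Inputs from the protocol article**

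- Clinical pregnancy 15% control and 30% active (Sample size). This reads the increase as 15 percentage points.
- 135 per arm, or 169 per arm with the 20% dropout allowance: 135 / 0.80 = 168.75, rounded up to 169, and 2 × 169 = 338, as stated. The figure of 135 itself is reproduced only approximately, at 134, by the pooled two-proportion formula with continuity correction. The printed formula gives (0.30 × 0.70 + 0.15 × 0.85) × (1.96 + 0.84)² / 0.15² ≈ 118. That is a separate matter. The planned 135 and 169 are used here only as arm sizes.
- Two-sided 5% level (Statistical methods).

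**Assumptions, because the article gives no such rates**

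- m, the share of clinical pregnancies that are multiple: 10%, 20% or 30%, equal in both arms.
- b, the proportion of women with any other AE: 5%, 10% or 20%, equal in both arms and independent of multiple pregnancy.
- The pregnancy rates are applied per woman. The article defines the outcome per embryo transfer cycle, so the rate per randomised woman may differ.

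**Step 1: AE probability in each arm.** With pregnancy rate π,

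P(any AE) = 1 − (1 − π·m)(1 − b).

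For m = 20%, multiple pregnancy alone is 0.15 × 0.20 = 3% in control and 0.30 × 0.20 = 6% in the active arm. With b = 5%:

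- control: 1 − 0.97 × 0.95 = 7.85%
- active: 1 − 0.94 × 0.95 = 10.7%

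**Step 2: rejection rate of the total-AE chi-square test.** Exact enumeration of the Pearson test without continuity correction; ranges run from 135 to 169 per arm.

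| Multiple share m | b = 5% | b = 10% | b = 20% |
|---|---|---|---|
| 10% | 7–8% | 6–7% | 6% |
| 20% | 13–15% | 10–11% | 8% |
| 30% | 20–24% | 15–17% | 11–12% |

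With multiple pregnancy removed, the rate returns to about 5%. Almost all of the excess lies in the direction of more AEs on electro-acupuncture.

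**Step 3: the IVF-ET class alone.** Its background is smaller than that of the total, so the tilt is at least as large. With m = 20% and 2% other IVF events, the proportions are 1 − 0.97 × 0.98 = 4.94% and 1 − 0.94 × 0.98 = 7.88%. The test rejects in 16–19% of trials.

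**Step 4: sensitivity to the size of the benefit.** At 15% vs 22.5% pregnancy, m = 20% and b = 10%, the total test rejects in only 6–7% of trials.

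**Step 5: what pooling does to a real needling excess.** Take needling events at 5% vs 15%, leave multiple pregnancy aside, and let other IVF events be equal in the two arms.

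| Comparison | Proportions | Power |
|---|---|---|
| Needling class alone | 5% vs 15% | 81–89% |
| Total, with 10% IVF events | 14.5% vs 23.5% | 48–57% |
| Total, with 20% IVF events | 24% vs 32% | 31–37% |

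The loss of power is confined to the total.

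**The case against.** **A reader might infer that the plan would miss real needling harm.** The article does not support that. It says "Adverse events (AEs) will be classified", lists needling events as their own class, and the sentence that tests the total goes on to test differences between the classifications. On the natural reading the needling class is compared between arms by itself, with the 81–89% power shown above. It contains no pregnancy event. The wording is loose, since it could also mean comparing one class with another, but that calls for clarification and does not show that the comparison is absent.

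**A reader might also treat the total as the headline safety test.** The article gives it no priority and no decision rule.

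**The extra rejections are not type I error in the strict sense.** If multiple pregnancies per randomised woman differ, the arms do differ in a listed event. A total that includes risks of conceiving is a legitimate all-cause safety measure. This stands. The difficulty is attribution: the objective concerns electro-acupuncture, and the total cannot separate its harm from its success.

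**The tilt and the dilution are not both large at once.** The tilt needs rare other AEs, and the dilution needs common ones. With the Step 5 background (5% needling plus 10–20% IVF events, so b of 14.5–24%) and m = 20%, the tilt is only about 7–9%. This also stands.

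**The time window is unclear.** The section says "The percentage of AEs and severe adverse events that occurred during treatment will be recorded in detail". If that meant only the acupuncture course, a pregnancy after IVF-ET would fall outside. But IVF-ET events are listed as AEs and events are also sought at follow-up visits, which argues against that reading. If exclusion is meant, the text should say so.

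**Conclusion.** The point holds for the total and for the IVF-ET class. As written, both include an event that can only follow the primary efficacy outcome, and both can reject because pregnancy rises.

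Under the full design effect the size is modest unless other AEs are rare or multiple pregnancies common. For the total test it is about 6–8% of trials if 10% of pregnancies are multiple, and about 8–15% if 20% are, for other AEs between 20% and 5%. These figures rest on assumed rates, equal in the two arms and independent, and they shrink with a smaller benefit.

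The point does not extend to a claim that needling harm would go undetected: the class comparison covers it, and dilution affects the pooled total only. The matter deserves correction because the event list and the test are both fixed in the text and the remedy is nearly free.

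**What to change.** In the Adverse events section:

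1. Take multiple pregnancy out of the tested AE total and out of the IVF-ET class. Keep recording it, and report it with the pregnancy outcomes, both per clinical pregnancy and per randomised woman.
2. State that each AE class is compared between arms, and that the electro-acupuncture class is the comparison that answers the safety objective.
3. The pooled total may stay as a supporting all-cause comparison, shown with and without multiple pregnancy.
4. State which treatment period the AE percentages cover.

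The cost is one moved table row, one extra line of analysis and a few words of clarification. Data collection and sample size do not change.

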### Criteria for discontinuing interventions

Acupuncture will be ended if participants meet any of the following conditions: (1) serious adverse events occurred during or after treatment, (2) misdiagnosed after randomization, and (3) patients found to be pregnant after randomization.

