In recent years, as an important part of traditional Chinese medicine, acupuncture has attracted tons of attention in the fields of reproductive endocrine and infertility worldwide [2–4]. Acupuncture can stimulate the neuro-endocrine system, regulate the overall endocrine level and ovarian microenvironment as a whole, improve the internal environment of follicles, improve ovarian hemodynamics, and thereby promote follicular development and ovulation. In addition, acupuncture can also enhance endometrial receptivity and relieve patients' tension and anxiety in assisted reproductive technology (ART) [5]. Acupuncture, which can improve ovarian function, is now widely used in the treatment of POF. Two Meta-analysis show that acupuncture is a relative effective intervention treating POF, which helps for recovering menstruation and boosting level of serum follicle-stimulating hormone (FSH) and estradiol (E2). The curative is sustainable till a month after the end of treatment [6, 7]. Since DOR can develop to POF within 1–6 months, why do not we intervene it in the early DOR phase in order to delay or reverse the progress to POF?

Given its effect on ovarian function, acupuncture is expected to be a new option for the treatment of DOR. But to date, the available evidence of the efficacy of acupuncture or electro-acupuncture for DOR remains insufficient. Only a few small sample, non-randomized controlled clinical trials suggest that acupuncture or electro-acupuncture can improve ovarian reserve function of DOR patients [8, 9]. Therefore, a large sample, multicenter, randomized controlled trial is designed to evaluate the efficiency and safety of electro-acupuncture in DOR patients. The clinical pregnancy rate is the primary outcome reflecting ovarian function. The following outcome of IVF-ET will also be evaluated as a secondary outcome.

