### Interventions

To improve patients’ adherence to interventions, electro-acupuncture will be performed by acupuncturists with over 5 years of clinical acupuncture experience and obtained a license from the Ministry of Health of the People’s Republic of China. Before performing the treatment, acupuncturists will receive centralized training including an introduction to the basic clinical research methods and a practical demonstration of the treatment. WeChat will also be used for making appointments and regular reminders. At each part of the study, including assessing ovarian function before and after the intervention, performing electro-acupuncture, or making follow-up visits, the independent gynecologist will make appointments and remind participants of some notes by using this APP.

The treatments of both two groups start after a spontaneous period or a withdrawal bleeding by progestin. For patients with amenorrhea or oligomenorrhea, the withdrawal bleeding is induced using progesterone by the outpatient doctors, and then the intervention starts after the withdrawal bleeding. The acupuncture protocols are formulated according to the theory of traditional Chinese medicine. The number of needles used, methods of stimulation (manipulation and electro-acupuncture), frequency, and time of the treatment are detailed described following the CONSORT and STRICTA recommendations [10].

Fixed protocols are used for both the treatment group and the control group. All patients receive the treatment of active acupuncture or sham acupuncture, twice or three times a week with a maximum of 24 times in 8-12 weeks. Treatments will not be performed during menstruation in both two groups. The treatment date, time, the name of the acupuncturist and the intensity of the electro-acupuncture stimulation which can vary between the different electrodes are recorded when the patient receives acupuncture treatment. The range of the intensity of the electro-acupuncture stimulation will be recorded, e.g., 1.2–3.0 mA.

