#### IVF-ET treatment

After the acupuncture treatment, patients’ ovarian reserve function will be evaluated again, and then IVF-ET cycle treatment will be conducted. This will be performed by the reproductive medicine center according to the patients’ situation and the standard procedure.

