### Concomitant treatments

Drugs and other treatments, which may interface the evaluation of electro-acupuncture effect, will be discouraged. Discouraged treatments include sexual hormones, contraceptives, and herbs. If treatment not recommended in this trial has already been performed, relevant information should be recorded in the patient’s case report form.

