### Outcome measures

#### Primary outcome measure

The primary outcome is clinical pregnancy rate per cycle of IVF-ET after acupuncture (through study completion, an average of 1 year). Clinical pregnancy was defined by the presence of a fetal heartbeat at 6–7 weeks of pregnancy. The clinical pregnancy rate is the number of clinical pregnancies per embryo transfer cycles.

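### A pregnancy conceived after randomisation but before IVF falls outside both numerator and denominator of the primary outcome, which conflicts with intention to treat

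*Protocol article*

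**What the plan says.** All references are to the protocol article.

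- **Primary outcome measure.** "The primary outcome is clinical pregnancy rate per cycle of IVF-ET after acupuncture". The denominator follows: "The clinical pregnancy rate is the number of clinical pregnancies per embryo transfer cycles". The event itself is defined without regard to how conception came about: "Clinical pregnancy was defined by the presence of a fetal heartbeat at 6–7 weeks of pregnancy".
- **Interventions.** Both arms are treated "twice or three times a week with a maximum of 24 times in 8-12 weeks".
- **IVF-ET treatment.** "After the acupuncture treatment, patients’ ovarian reserve function will be evaluated again, and then IVF-ET cycle treatment will be conducted". IVF therefore comes after the course.
- **Criteria for discontinuing interventions.** One reason to end acupuncture is "patients found to be pregnant after randomization". The section says nothing about how such a pregnancy is analysed.
- **Concomitant treatments.** "Discouraged treatments include sexual hormones, contraceptives, and herbs".
- **Background and Objectives.** Acupuncture is expected to regulate the ovarian environment and "thereby promote follicular development and ovulation". The first hypothesis takes the clinical pregnancy rate as the reflection of ovarian function.
- **Statistical methods.** All analyses follow intention to treat, and missing data are multiply imputed.
- **Follow-up detection.** Pregnant women are followed to the end of pregnancy, under the secondary outcomes.

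**The concern.** There is a window of 8 to 12 weeks between randomisation and IVF in which a woman under 40 can conceive. The discontinuation criteria allow for a pregnancy being found then, but the primary outcome has no place for it. She has had no transfer, so she adds nothing to the denominator, and her pregnancy did not arise from IVF, so it adds nothing to the numerator.

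Two things are at stake. First, whether a randomised woman enters the primary comparison depends on something that happens after randomisation and that the treatment is supposed to influence. The two sets of women with a transfer are then no longer the groups that randomisation created. Second, the event that removes her is the kind of result the rationale predicts. If the active arm has more such pregnancies, the primary rate can miss part of the benefit.

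The intention-to-treat statement does not repair this, because it cannot put a woman without a transfer into a rate per transfer. If she were instead treated as missing, multiple imputation would replace an observed pregnancy with a modelled IVF result.

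**Working it through.** **1. The plan's own figures.** Sample size assumes 15% in control, an increase of 15 points (so 30%), two-sided alpha 0.05 and 80% power, and states 135 per group. The allowance for 20% dropout reproduces: 135 / 0.80 = 168.75, rounded up to 169 per group, or 338 in total. The printed formula does not return 135 at these rates: (0.15 × 0.85 + 0.30 × 0.70) × (1.960 + 0.842)² / 0.15² = 117.7, so 118. A continuity-corrected formula gives 134. That is a separate matter. Here 135 is taken as the planned evaluable number per arm.

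**2. Tracing one woman through the definitions.**

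| Step | Numerator | Denominator |
|---|---|---|
| Randomised, starts the course | – | – |
| Found pregnant during the course, acupuncture ends | not a pregnancy from IVF-ET | no transfer cycle |
| Fetal heartbeat at 6–7 weeks | still not counted | still none |
| Pregnancy fails, later has a transfer | only an IVF pregnancy counts | enters here |

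**3. Size, under stated assumptions.** The article gives no natural conception rate, so the rates s are assumed. Let total clinical pregnancy per woman be 15% (control) and 30% (active), natural conceptions included, with 135 women per arm.

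With exclusion as written, each arm's rate is (total − s) / (1 − s) on 135 × (1 − s) women. Power = Φ(difference / SE − 1.96), with SE = √[p₀(1 − p₀)/n₀ + p₁(1 − p₁)/n₁].

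- *All pregnancies count:* SE = √[(0.1275 + 0.21)/135] = 0.0500; 0.15/0.0500 = 3.00; power 85%.
- *2% vs 4%:* 0.13/0.98 = 13.3% on 132.3 women; 0.26/0.96 = 27.1% on 129.6. Difference 13.8 points, SE 0.0489, ratio 2.82, power 81%.
- *2% vs 6%:* 13.3% on 132.3; 0.24/0.94 = 25.5% on 126.9. Difference 12.3 points, SE 0.0487, ratio 2.52, power 71%.
- *2% vs 2%:* 13.3% vs 0.28/0.98 = 28.6%. Difference 15.3 points, so no reduction.

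**4. A different assumption.** Suppose IVF success among the women who do not conceive naturally is still 15% vs 30%. Exclusion then leaves the difference at 15.0 points whatever the natural rates. At 3% vs 6% the numbers fall to 130.95 and 126.9, SE is 0.0513, the ratio 2.93 and power 83%, against 85% with no natural conceptions. Counting those pregnancies as successes would give 0.03 + 0.97 × 0.15 = 17.6% vs 0.06 + 0.94 × 0.30 = 34.2%, a difference of 16.7 points (from unrounded rates).

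**5. Scoring as failure, for comparison only.** If the denominator became all randomised women and the numerator stayed IVF-only, the totals in step 3 would give 13% vs 26% (13 points, 78% power) and 13% vs 24% (11 points, 65%). The article does not state that rule.

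**The case against.** The best defence is that an IVF-conditional endpoint answers a question the trial asks. Participants are enrolled to undergo IVF-ET, and the abstract names the IVF outcome among the aims. Natural pregnancies are not lost as data either, since pregnant women are followed to the end of pregnancy. This stands as a reason to keep the per-transfer rate as a secondary outcome. It does not reconcile that rate with intention to treat, or with a hypothesis about ovarian function.

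A second defence is that an article may leave the handling of such events to the full protocol or the SAP. That would hold if the article were silent. It is not: it states the numerator and denominator of the primary rate, and these leave the woman out.

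Other cautions stand and limit the point:

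- Contraceptives are listed beside sex hormones and herbs, as treatments that might interfere with the evaluation. This may mean hormonal contraceptives as confounders. It does not show that couples are asked to try to conceive, only that conception is not ruled out.
- The discontinuation criterion may also cover a pregnancy already present at randomisation and found later.
- The criterion ends acupuncture only. A reader might infer that such a woman never has IVF, but one whose pregnancy fails could still have a transfer.
- A reader might infer that these women are scored as failures, with power falling to 78% or 65%. Those figures need a denominator of all randomised women, which the article does not use.
- A reader might infer that the women lost have the best prognosis, or that the primary comparison is always biased towards no effect. Nothing in the article supports the first, and the second depends on the assumed rates.

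**Conclusion.** The point holds as a flaw in the stated endpoint definition. A pre-IVF pregnancy cannot be a primary success, and the woman leaves the analysis unless she later has a transfer. This conflicts with the intention-to-treat statement and fits poorly with the objective. It is not independent of the choice of denominator: it is one consequence of using a rate per transfer.

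The size is unknown and may be small, because every natural conception rate used here is assumed. With fixed totals of 15% vs 30%, the difference falls by 1.2 points at 2% vs 4% and by 2.7 points at 2% vs 6%, and power falls by about 4 and 14 points. With equal natural conception, or with IVF success unchanged among the remaining women, the difference is not reduced, though the comparison still rests on women selected after randomisation. The rule should be changed, but no particular loss of power can be claimed.

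**What to change.** Before unblinding, amend the primary outcome definition as follows:

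- **Unit and denominator:** each randomised woman.
- **Success:** a clinical pregnancy by the existing heartbeat criterion, conceived after randomisation, either before IVF or from the IVF-ET cycle. The denominator has to change together with the numerator. Adding pre-IVF pregnancies to a count of transfer cycles would not give a proportion.
- **Missing data:** women with an observed pre-IVF pregnancy are not imputed.
- **Secondary outcome:** the per-transfer IVF rate as now defined.
- **Reporting:** pre-IVF conceptions listed by arm.

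No change to the discontinuation criteria is proposed. The data should already be available, since pregnancy ends acupuncture and pregnant women are followed. There are two costs: the primary outcome is no longer purely an IVF outcome, which the secondary rate covers, and a recruiting trial needs an amendment to its endpoint definition. Fixing the rule before unblinding keeps the choice from depending on the counts seen in each arm.
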